### Intervention and comparison condition

#### Standard care

As noted, in South Australia all families of newborns are offered a clinic or home-visit by a Child and Family Health community nurse during the initial postnatal weeks. The aim of the home-visit is to: (i) complete maternal and child health checks, (ii) provide comprehensive, information-based support to families of new infants, (iii) offer guidance and information about future child development, and (iv) link families to other services where this is required [24]. As this service is offered to all families of newborns in South Australia, it is relatively expensive involving more than 18,000 visits to homes across the State annually with each visit lasting about 60–90 mins. Although clinic visits are an option (or a visit in a ‘safe place’ for women who are considered not safe enough to visit at home) most parents prefer a home visit. Following this visit, mothers are encouraged to bring children for health checks at community clinics when the children are aged 6 and 18 months. A range of other services are also available at over 120 clinic sites across South Australia, with additional support including a telephone helpline, day-long support at community clinics for parents who need additional support with problems such as feeding or settling; and residential care for families with major unresolved problems with infant feeding, settling, and sleeping problems.

#### Nurse led group-based internet program

Following their first contact with the Service, all mothers in the intervention were assigned to an internet-based mothers’ group comprised of 12 mothers of similar-aged infants moderated by a trained Child and Family Health community nurse. The internet-based groups function in a comparable fashion to “chat rooms” found on many internet sites. However in the present intervention, all groups are nurse-moderated. Nurses utilise the group format to: (i) provide information directly to mothers, guided by a curriculum widely utilised in CaFHS face-to-face parenting groups, (ii) respond to questions asked by mothers, (iii) sensitively correct misperceptions and misinformation arising during discussion and exchange of information by mothers, and (iv) direct mothers to additional information sources both within the intervention website and via hyperlinks to other websites approved by CaFHS in SA.

The content of the intervention, established as a part of this project, addresses three broad issues: (i) steps that mothers can take to resolve common practical problems experienced by mothers of young children (e.g., feeding, sleeping, and “settling”), (ii) approaches that mothers can take to look after their own health and well-being, including problems with mood and depressive symptoms, and (iii) activities that mothers can use to promote the health of their infants (e.g., improving parent-infant attachment, stimulating infant language development). In the intervention mothers are guided to information relevant to infants at different stages of development within this period (e.g., 6 weeks, 4 months, and 6 months). We believe that this is important because clinical experience suggests that mothers want information specifically relevant to the age of their infant, rather than more broadly-based anticipatory advice about what might occur in the future.

The ‘mother’s view’ of the website is comprised of four components accessed by browser tabs: (i) Home Group - contains the chat room and also displays profile pictures (when supplied by participants) of other group members. Mothers’ and nurses’ posts and comments in the chat room are visible to all group members. The format of the chat room is similar to Facebook as this is familiar to many mothers, (ii) Milestones and Reminders - provides an interactive display of child developmental milestones and health reminders that can be printed locally. It also contains an interactive events calendar displaying topics that nurses will discuss, and other material relevant to the functioning of the group, (iii) Resources – contains ‘Frequently Asked Questions’ grouped into topic areas that parallel the topics in the curriculum used by nurses. Nurses can direct mothers to relevant resources as required or mothers can find information themselves, and (iv) Contacts and Assistance – contains a list of useful contact numbers and provides a portal through which mothers can privately message their group’s nurse.

The ‘nurses’ view’ of the website is comprised of three main elements: (i) Group Dashboard -which displays information about individual groups such as group activities, nursing notes maintained by nurses, and responses to quizzes posted by nurses to check maternal knowledge and to stimulate discussion between mothers, (ii) Parent Dashboard - which displays information about individual parents including parent case notes, individual website login activities (e.g., where parents view material but don’t post a message), and notifications that mothers have added information about children’s milestones, and (iii) Nurse Home Group page - through which nurses access their group’s chat room but also contains additional resources that nurses utilise (e.g., information inserted into the group chat room such as messages, reminders, and short quizzes).

### Measures

Maternal and infant outcomes in all groups are being evaluated using age-appropriate questionnaires completed when infants are aged <2 months (pre-intervention), 9, 15 and 21 months. Questionnaires are administered by trained research assistants in mother’s homes or at another convenient location chosen by mothers. The measures in the various domains below were selected based on their wide use, validity, reliability, and comparability with data collected in the Longitudinal Study of Australian Children (LSAC) [25].

#### Primary outcomes

##### Quality of maternal parenting

*Parenting Stress Index* (*PSI*): The PSI is a widely used questionnaire designed to assess parent and child characteristics relevant to “parent–child systems” [26]. Items consist of statements with a five-point response scale with endpoints labelled ‘Strongly Agree’ and ‘Strongly Disagree’. Relevant scales assess maternal perceptions of parenting competence, the quality of parent–child relationships, and the impact of parenting responsibilities on autonomy and self-identity. We utilise the five scales from the PSI labelled Competence, Isolation, Attachment, Role Restriction, and Spouse. Each of these scales assesses an aspect of parenting which is an important goal for CaFHS services.

*LSAC Parenting Assessment Measures:* The questionnaires employed in LSAC are being utilised to assess parental warmth, parental irritability, and parental sense of self-efficacy [27]. Level of parental warmth is based on six items that assessed the frequency with which expressions of warmth, happiness or affection occurred in the mother-infant relationship. Mothers respond using a 5-point response scale on which the endpoints are labelled “never/almost never” to “always/almost always”. Level of irritability is based on five items that assess the frequency with which expressions of anger or irritability occurred in the mother-infant relationship. Mothers respond using a 10-point response scale on which the endpoints were labelled “not at all” to “all the time”. Finally, level of parental self-efficacy is based on four items that assess mothers’ perceptions of their ability to manage their child in different circumstances. Mothers respond using a 10-point response scale on which the endpoints were labelled “not at all how I feel” and “exactly how I feel”.

#### Secondary outcomes

##### Infant-mother attachment relationship

*Parenting Stress Index (PSI) Attachment Scale:* The Attachment scale of the PSI assesses the quality of the mother-infant attachment relationship.

#### Infant social and emotional development

*Ages and Stages Questionnaire - Social-Emotional (ASQ:SE):* The ASQ:SE is used to measure the social and emotional development of infants [28]. Questionnaire items address: self-regulation, compliance, communication, adaptive functioning, autonomy, affect, and interaction with people. The ASQ: SE is comprised of eight questionnaires containing items developmentally appropriate for children aged 6, 12, 18, 24, 30, 36, 48, and 60 months. Each questionnaire can be used within 3months for children aged 6 through 30 months and within 6months for children aged 36 through 60 months. The 6-, 12-, 18- and 24-month questionnaires are being utilised in the present study. The number of items comprising the questionnaires range from 19 items on the 6-month questionnaire to 26 items on the 24-month questionnaire. All the questionnaires use a 3-point response scale on which responses are labelled “most of the time”, “sometimes”, or “rarely or never”.

#### Infant communication development

*Communication and Symbolic Behaviour Scales Developmental Profile - Infant/Toddler Checklist (CBS-DP):* Infants’ communicative abilities and symbolic ability will be assessed using the 24-item CBS-DP [29]. The measure provides a total score which can range from 0–57, as well as composite scores for the domains of social, speech, and symbolic skills. These domains are broadly related to infants’ pre-linguistic abilities (e.g., emotion, use of eye gaze, and gestures), linguistic abilities (e.g., use of sounds and words), and cognitive abilities (e.g., understanding of words and use of objects). The instrument has sound psychometric properties and normative data are available from LSAC (Commonwealth of Australia, 2011).

#### Parents’ perceptions of the quality of nursing support

Parents’ perceptions about the quality of the support provided by nurses will be assessed using a questionnaire specifically developed for this purpose. This will enable comparison of parents’ perceptions of the quality of nurse support in the nurse led internet-based program versus home-based visit. The questionnaire is comprised of 18 items which ask about the level of helpfulness of the nurses, the quality of the parent-nurse relationship and the extent to which mothers understood the goals of the program with which they were involved [30,31].

#### Service utilisation

We are identifying utilisation of community and clinic-based services by infants and mothers by means of standard questionnaires employed in the LSAC [27] and the National Child and Adolescent Mental Health Survey [32]. These items identify: (i) services used by mothers for their child during the previous 12 months, (ii) whether there are other services that children needed but could not access, and (iii) reasons why their child is unable to access needed services.

#### Demographic information

Background information is obtained about participating infants and their careers, including children’s age and gender, parental education and employment, housing, financial strain, and family characteristics (e.g., single-parent or two-parent; and the number and age of dependent children living in the household).

### Analysis plan

Primary analyses will be by intention-to-treat. For interim analyses, outcomes measured at one point in time during follow-up will be compared using linear or log binomial regression. For longitudinal analysis we will use Generalized Estimating Equations (GEE) to fit random effects regression models to describe the effects of the intervention on outcomes. GEE models are a flexible structure that allows parameter estimation accounting for temporally correlated outcome data and design effects due to clustering by nurse, although as a proportion of total variance, clustering is often found to be small [33]. Comparison of the randomized versus observational groups will be conducted by pooling the whole study population and including dummy variables (and potentially interactions with time and baseline psychosocial adversity) indicating randomized versus preference-based participation in the nurse led internet-based program.

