We are using a preference-based design [21] in which service preferences are elicited from mothers at the time that they are recruited to the study. Mothers who express a “strong preference” for the intervention or for standard care are allocated to their preferred group. Mothers without strong preferences are randomized to intervention or standard care (Figure 1). The advantage of this approach is that many people refuse randomization, and/or drop out post randomization (if they don’t get their preferred service). As such, results can only be generalized to those who participate in randomization and complete the study (as low as 35% in some studies [21]). We have included those with a strong preference in this study as an “observational” cohort so we can compare outcomes in those randomized, with those who chose randomization or standard care, and thus improve generalizability of the findings to the whole population for whom the service is intended. If outcomes are similar in the randomized and preference groups then we can more clearly make inferences about the effects in the whole population.

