### Sample size

Our primary outcomes focus on mothers’ sense of competence and self-efficacy in areas relevant to parenting and problem solving with infants. These outcomes were chosen in consultation with CaFHS nurses who identified one of their primary goals as helping ensure parents feel more competent to manage challenges associated with the care of infants.

Given that the primary question for the trial focuses on testing the equivalence of the nurse-moderated group-based internet program versus standard care, we estimated that with a sample size of 200 per randomized group, we would have 80% power at alpha = 0.05 to detect a 0.25 standard deviation difference (inferiority range) between the home-visit and nurse led internet groups in the primary outcome. Thus we would have 80% power to test the hypothesis that the internet-based intervention is no more than 0.25 of a standard deviation inferior when compared to standard care on the primary outcome measures. These estimates were based on data from our current 2 year follow-up of the Nurse Home Visiting program [11]. Based on this earlier study we allowed for an attrition of 20% over 2 years in the present study. To take this into account, we aimed to recruit 240 mothers to be randomised to each study group. Figure 1 shows the participant flows in the study leading to the final trial sample.

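### GEE is named for a longitudinal non-inferiority comparison that allows for 20% attrition; a likelihood-based mixed model with the baseline score would guard better against score-related dropout that differs between arms

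*Protocol article*

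**What the plan says.** The Analysis plan section of the Protocol article makes the primary analyses intention-to-treat. It names GEE for the longitudinal analysis, reasoning that "GEE models are a flexible structure that allows parameter estimation accounting for temporally correlated outcome data" and can also absorb clustering by nurse. It describes GEE as the means of fitting random-effects regression models.

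The Sample size section sets the target: to show that "the internet-based intervention is no more than 0.25 of a standard deviation inferior when compared to standard care", with 80% power at alpha 0.05, "with a sample size of 200 per randomized group". On loss it says "we allowed for an attrition of 20% over 2 years in the present study", a figure taken from an earlier home-visiting study, and therefore "we aimed to recruit 240 mothers to be randomised to each study group".

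The Measures section places assessments at under 2 months (pre-intervention) and at 9, 15 and 21 months. A mother who leaves will therefore usually have earlier scores on file.

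**The concern.** GEE without weighting or imputation estimates each visit's mean from the mothers still present. It borrows from earlier scores only as far as the working correlation lets it. When the chance of leaving depends on earlier scores, those means can drift. If the drift is the same in both arms, it largely cancels in the difference. If it is not, the difference is biased.

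The two services differ in kind (a six-month online group against a single visit plus services on request), so unequal patterns of loss are conceivable. In a non-inferiority comparison one direction matters most. If struggling mothers leave the internet arm selectively, that arm looks better than it is and the estimate moves inside the margin. Calling the analysis intention-to-treat does not bring back scores that were never collected.

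**Working it through.** **1. The plan's own figure.** Inputs from the Sample size section: margin 0.25 SD, power 80%, alpha 0.05. With a one-sided test and no true difference, n = 2 × (1.645 + 0.842)² / 0.25² = 198 per group, against 200 stated. A one-sided 0.025 test would need 252, so the one-sided 5% reading is used below. Losing 20% of 240 leaves 192 per group.

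**2. From bias to error rate.** Put the true difference exactly at the margin, -0.25 SD, with scores oriented so that higher is better. With 192 per group the standard error of an unadjusted comparison is √(2/192) = 0.102 SD. The chance of wrongly declaring non-inferiority is about Φ(bias/0.102 - 1.645), which is 5% when the bias is zero.

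- Bias 0.083: Φ(0.82 - 1.645) = 20%
- Bias 0.119: Φ(1.17 - 1.645) = 32%
- Bias 0.13: Φ(1.27 - 1.645) = 36%

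**3. Size of the bias.** This needs simulation. Assumptions that are not in the article: correlation 0.6 between all visits; monotone dropout; chance of leaving dependent on the last observed score in the internet arm and random in standard care. There were 240 mothers per arm. Cells give the false non-inferiority rate at 21 months, 1,000 runs each; Monte Carlo error at 5% is about ±1.4 points.

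| Loss by 21 months | Odds ratio of leaving per SD lower last score | Independence | Exchangeable, follow-ups only | Exchangeable within mother + baseline |
|---|---|---|---|---|
| 20-22% | 1.5 | 15% | 7% | 5% |
| 20-22% | 2 | 24% | 9% | 4% |
| 20-22% | 2.7 | 38% | 12% | 6% |
| about 20% in each arm | 1.5 | 11.8% | 6.4% | 4.5% |
| about 20% in each arm | 2 | 19.3% | 8.1% | 4.6% |
| about 20% in each arm | 3 | 30.3% | 10.3% | 4.8% |

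The last two rows correspond to independence biases of 0.083 and 0.119 SD, so they agree with step 2. A further 500 runs per scenario gave 26-42%, 10-12% and 5-6% for the three methods. In another set at an odds ratio of 2.7, independence GEE estimated -0.12 SD (35%), exchangeable GEE -0.21 SD (11%), and a likelihood-type analysis using all earlier scores -0.25 SD (about 5%).

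**4. Sensitivity to the assumptions.**

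- Equal selection in both arms: 4.4-4.9% in one set, 5-6% in another, and about 7% with independence GEE in a third.
- Autoregressive correlation 0.7, internet arm only, odds ratios 1.5 to 3: independence 10.5-24.3%, exchangeable on follow-ups 5.9-7.2%, exchangeable plus baseline 5.2-5.9%, unstructured plus baseline 5.0-5.1%.
- Opposite selection in the two arms (odds ratios 2 and 0.5): independence 40-50%, unstructured plus baseline 4.9-5.7%.
- Selection in standard care only: by symmetry, the bias runs against non-inferiority.

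**5. Why the working correlation matters here.** The plan wants the same GEE to handle clustering by nurse. Suppose the nurse were made the cluster, with one exchangeable correlation, 12 mothers per nurse (one group; the caseload is not stated), three follow-ups and no nurse effect. There are then 36 × 35 / 2 = 630 pairs of scores, of which 12 × 3 = 36 lie within a mother. The common correlation becomes 0.6 × 36/630 = 0.03, close to independence. Simulated rates were 14%, 24% and 37% at odds ratios 1.5, 2 and 2.7.

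**The case against.** The strongest reply is that the article never commits to the vulnerable form of GEE. It states no working correlation, weighting, baseline adjustment or imputation. An article commonly leaves these to the full protocol or SAP, so their absence is no finding. It also speaks of random-effects models, which could mean something near the remedy proposed here. That stands: the point concerns the suitability of the named method, and GEE set up with mother-level correlation and the baseline score comes out close to nominal.

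Three stronger readings are tempting, and the article does not support them.

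- *The plan itself predicts preference-driven dropout.* The Study design section does say that "many people refuse randomization, and/or drop out post randomization" when they miss their preferred service. It says so about trials in general, to justify the preference design. Here mothers with a strong preference receive their choice, and only those without one are randomised. The passage is not evidence of such loss in the randomised arms.
- *GEE is unbiased only if dropout is unrelated to earlier scores.* This is too absolute. A near-correct working correlation with baseline adjustment, weighting, or prior multiple imputation can each make it valid or nearly so.
- *The bias will favour the internet arm.* Nothing in the article shows that loss differs between arms, or in which direction.

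**Conclusion.** The point holds as an inexpensive strengthening of the analysis, not as an error in the plan. Under selective loss in the internet arm only (odds ratios 2 to 2.7, correlation 0.6, 20-22% loss), false non-inferiority at the margin is roughly 25-40% with independence GEE and 10-12% with exchangeable GEE on follow-ups. It is about 5-6% with mother-level correlation plus baseline or a likelihood-based analysis. Holding loss at about 20% in each arm lowers the first figure to about 19% at an odds ratio of 2 and 30% at 3. The dropout odds ratios, the correlations and the difference between arms are all assumptions; with equal selection the error stays near nominal. The margin, group sizes, attrition allowance and choice of GEE come from the article.

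**What to change.** For the primary longitudinal comparison, specify a likelihood-based linear mixed model that includes the baseline score, with unstructured within-mother covariance and arm-by-time terms. If GEE is to be kept, precede it with multiple imputation, done separately by arm, from the baseline and all earlier follow-up scores.

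Add one tipping-point sensitivity analysis: shift the imputed scores of internet-arm dropouts downwards until non-inferiority is lost, and report that shift in SD units. Readers can then judge whether so large a departure is believable, which also covers dropout that depends on unobserved scores.

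The cost is a change of wording and a little more programming, with a somewhat wider interval in the sensitivity analysis. No new data are needed, and the Objectives section says follow-up was still under way at publication.

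### The randomised-versus-preference analysis, read literally, compares outcome levels, whereas the generalisability argument needs the arm effects to agree; an arm-by-cohort term should be specified

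*Protocol article*

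**What the plan says.** Under Study design, the protocol article describes two cohorts. "Mothers who express a “strong preference” for the intervention or for standard care are allocated to their preferred group"; the remaining mothers are randomised. Preference mothers therefore occur in both arms, and the design has four cells.

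The preference mothers are kept in the study and labelled observational. The reason given is: "so we can compare outcomes in those randomized, with those who chose randomization or standard care, and thus improve generalizability of the findings". (In that sentence, choosing randomisation presumably means choosing the internet programme.) The inferential rule follows: "If outcomes are similar in the randomized and preference groups then we can more clearly make inferences about the effects in the whole population".

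The Analysis plan implements this in one model fitted to all participants together, which it describes as: "including dummy variables (and potentially interactions with time and baseline psychosocial adversity) indicating randomized versus preference-based participation in the nurse led internet-based program". The only interactions listed are with time and baseline adversity, and both are optional.

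The Sample size section sets the scale for the primary question: "with a sample size of 200 per randomized group, we would have 80% power at alpha = 0.05 to detect a 0.25 standard deviation difference", so as to test that "the internet-based intervention is no more than 0.25 of a standard deviation inferior when compared to standard care".

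**The concern.** The rule starts from outcomes and ends with effects. Extending the trial result beyond randomised mothers requires the internet-minus-standard difference to be about the same in both cohorts. Mothers with strong preferences chose their group and may well differ in prognosis, so their outcome levels can differ from those of randomised mothers for reasons unrelated to the intervention. Equally, overall levels can coincide while the effects differ.

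The listed interactions do not close the gap. Cohort by time compares trajectories, and cohort by adversity compares subgroups. Neither is a difference in arm effects unless arm is also in the term.

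What is at stake is the stated reason for enrolling the preference cohort, which is to inform a service offered to all mothers. As written, the comparison could support or weaken the extension for reasons that have little to do with the effect of the programme.

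**Working it through.** Notation: R1 and R0 are the mean outcomes of randomised mothers on internet and standard care; P1 and P0 are those of preference mothers. All are in SD units. The quantity needed is D = (P1 − P0) − (R1 − R0).

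**Plan's own figure.** With a margin of 0.25 SD, 80% power and one-sided alpha 0.05, n = 2(1.645 + 0.842)²/0.25² ≈ 198 per group, against the stated 200. The article does not state sidedness, but this reading reproduces its figure, so 0.25 SD is used below as a yardstick.

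**What the participation dummies would estimate.** The cell means are illustrative. Cell sizes assume 240 per randomised arm (the target) and 819 − 480 = 339 preference mothers; the actual split is in Figure 1, which is not available to this review.

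- *Single cohort dummy, effects differ.* Take R1 = R0 = 0, P1 = −0.125, P0 = +0.125 and an even preference split. Both cohort means are 0 and the dummy is 0.000, yet D = −0.25. With P1 = −0.25 and P0 = +0.25, the dummy is still 0 and D = −0.50.
- *Uneven split, 70:30 towards internet.* Take P1 = −0.075 and P0 = +0.175, so the preference mean is 0 and D = −0.25. The arm weights within cohort are 240 × 240/480 = 120 and 237.3 × 101.7/339 = 71.2. The additive arm coefficient is 71.2 × (−0.25)/191.2 = −0.093, and the cohort dummy is 0 − (−0.093)(0.7 − 0.5) = 0.019.
- *Contrast among internet users only (P1 − R1).* In the first example this is −0.125, so it would show something. But take R1 = R0 = P1 = 0 and P0 = +0.25: the contrast is 0 while D = −0.25. Any cohort difference confined to standard care is missed.
- *Effects agree, levels differ.* Take R1 = R0 = 0 and P1 = P0 = 0.30. The dummy is 0.30 and D = 0.

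**Precision of D if it is specified.** SE = √(1/n_R1 + 1/n_R0 + 1/n_P1 + 1/n_P0), unadjusted and at one visit. The attrition allowance is the article's: "we allowed for an attrition of 20% over 2 years in the present study".

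- Completers: 240 × 0.8 = 192 per randomised arm; 339 × 0.8/2 = 135.6 per preference arm on an even split (assumed).
- SE = √(2/192 + 2/135.6) = 0.159. The 90% half-width is 1.645 × 0.159 = 0.26; the 95% half-width is 0.31.
- Preference split 70:30: SE 0.167, 90% half-width 0.27 to 0.28. Split 90:10: SE 0.227, 90% half-width 0.37.
- Adjusting for baseline score multiplies the SE by √(1 − r²). With r = 0.5 (assumed), SE = 0.159 × 0.866 = 0.137 and the 90% half-width is 0.23. On the even split the half-width equals 0.25 at r = √(1 − (0.25/0.261)²) ≈ 0.29.
- Power to detect D = 0.25 at two-sided 0.05, with 20% attrition and no adjustment: 35% on the even split, 20% at 90:10.

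**The case against.** The strongest reply is that the wording is loose rather than wrong. The Analysis plan refers to dummy variables in the plural and ties them to participation in the internet programme. A four-cell coding would fit those words, and D would then be an estimable contrast. If outcomes were compared within each arm and matched in both, equal effects would follow arithmetically. The article also condenses a fuller plan, and its list of interactions is provisional. All of this stands, and it is why the point is put as what a literal reading gives. It does not remove the point: the article names the terms it has in mind without arm among the interactions, and the Study design rule judges similarity of outcomes under any coding.

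Two further replies also stand. A reader might infer that a non-significant dummy would be taken as similarity, but the article states no significance test for this comparison. And the design already treats the preference mothers as observational, sizes the trial on randomised groups, and introduces pooling only for this comparison, so nothing suggests that preference mothers enter the primary result.

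Finally, 0.25 SD is a one-directional margin for the main effect. Using it as a tolerance for a difference between effects is a choice made here for scale, not something the article prescribes.

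**Conclusion.** The point holds in a limited form. The stated rule and the stated model do not target agreement of arm effects between cohorts. On the literal reading, the comparison can miss a 0.25 SD difference in effects, or signal a difference when the effects agree.

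A reader might go further and say that the preference cohort cannot support generalisation, or that agreement within 0.25 SD cannot be shown. The documents do not support either. The needed contrast is estimable from the four cells, and the 90% half-width of about 0.26 SD rests on an assumed 480/339 split, an even preference split, 20% attrition and no baseline adjustment. A baseline correlation above about 0.29 brings it inside 0.25 SD on the even split, while uneven preferences push it out again. The safe conclusion is that precision is limited, so a non-significant interaction should not by itself be read as agreement.

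The randomised non-inferiority comparison is not affected. This should be corrected because the extra purpose of the design depends on it.

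**What to change.** - In the pooled model, specify arm, cohort (randomised or preference) and arm by cohort, by visit, adjusted for baseline outcome score and the demographic and adversity variables already collected.
- Report the interaction with its confidence interval and the adjusted arm effect in each cohort.
- Reword the Study design rule so that its condition is similarity of the arm effects, judged from that interval against a limit stated in advance.
- State that the arm contrast among preference mothers is self-selected, and so supportive only, and that the primary result comes from randomised mothers.

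The cost is one model term (by visit) and some wording, with no new data. The price is a more modest generalisability claim, since the interval may be too wide to show close agreement.
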